## Abstract

**Background:**

It has been indicated that rotator cuff tears, especially large or massive ones, can cause suprascapular neuropathy. When such a diagnosis has been established, it is still unknown whether an arthroscopic release of the superior transverse scapular ligament during cuff repair can change the course of this neuropathy.

**Methods/design:**

This is a single-center, double-blinded randomized controlled trial for which 42 patients with large or massive repairable rotator cuff tears and suprascapular neuropathy will be recruited and followed up at 6 and 12 months. Nerve function will be measured by nerve conduction and electromyography studies preoperatively and at the selected follow-up periods. Patients will be randomly divided into equally numbered groups, the first one being the control group. Patients of this group will undergo arthroscopic repair of the rotator cuff without combined arthroscopic release of the superior transverse scapular ligament; in the second group the ligament will be released. The primary objective is to test the null hypothesis that arthroscopic repair of large/massive rotator cuff tears in patients with combined suprascapular neuropathy provides equivalent outcomes to one-stage arthroscopic cuff repair where the superior suprascapular ligament is additionally released. The secondary objective is to search for a relation between rotator cuff tear size and degree of suprascapular nerve recovery. The tertiary objective is to demonstrate any relation between rotator cuff muscle fatty infiltration grade and degree of suprascapular nerve function. Patients, clinicians during follow-up clinics and the neurologist will be blinded to the type of surgery performed.

**Discussion:**

To the best of our knowledge, we are unaware of any prospective, randomized double-blinded studies with similar objectives. So far, the evidence suggests a positive correlation between massive rotator cuff tears and suprascapular neuropathy. However, there is mixed evidence suggesting that neuropathy can be effectively treated with rotator cuff repair with or without release of the superior transverse scapular ligament.

**Trial registration:**

ClinicalTrials.gov registration number NCT02318381; date of initial release: 5 December 2014.

**Electronic supplementary material:**

The online version of this article (doi:10.1186/s13063-016-1672-y) contains supplementary material, which is available to authorized users.

## Background

Suprascapular nerve (SSN) neuropathy may be associated with a rotator cuff tear [1], especially tears bigger than 3 cm. Cofield classified rotator cuff tears as: small tear <1 cm, medium 1–3 cm, large 3–5 cm, and massive >5 cm [2]. The proposed mechanism involves nerve traction that is caused by tethering of the nerve against fixed location points; these are the major and minor scapular notches [3]. Radiographic methods, especially computed tomography (CT) and magnetic resonance imaging (MRI), are often used to evaluate atrophy of the rotator cuff. Fatty infiltration and atrophy may both be associated with a torn rotator cuff and SSN neuropathy [4–6].

Previous studies have reported a relation between SSN neuropathy and rotator cuff tears [7–10]. If these findings are proven accurate, they may represent an important step in optimizing treatment for rotator cuff tears. Nondiagnosed SSN neuropathy could affect the success rate repair of the cuff and further weaken the muscles innervated by this nerve. Theoretically, this neuropathy may be a contributing factor in the pathophysiological mechanism of fatty infiltration and, finally, cuff tear arthropathy although a linear relationship between the degree of neuropathy and the size of the rotator cuff tear has not been demonstrated [9].

Surgical techniques of treating SSN neuropathy in the setting of rotator cuff tears may include open or arthroscopic release nerve release. Open nerve release has provided good results in patients with SSN neuropathy by improving motor function of the rotator cuff muscles [11]. However, arthroscopic release techniques are currently gaining popularity as they can be combined with repair of the torn rotator cuff. They are also less invasive, provide better visualization and require less surgical time [1].

We searched the websites of online trial registries, “http://www.clinicaltrials.gov/,” “http://www.isrctn.com,” “http://onlinelibrary.wiley.com/cochranelibrary,” as well as “http://www.ncbi.nlm.nih.gov/pubmed.” To the best of our knowledge, there are no randomized prospective studies that compare the outcome of SSN neuropathy after arthroscopic dissection of the transverse scapular ligament in patients with a torn rotator cuff against control groups that did not undergo ligament dissection. We are also unaware of any studies that aimed to find any relation between the degree of neuropathy and the size of the rotator cuff tear. The primary objective is to test the null hypothesis that arthroscopic repair of large/massive rotator cuff tears in patients with combined suprascapular neuropathy provides equivalent outcomes to one-stage arthroscopic cuff repair where the superior suprascapular ligament is additionally released. The secondary objective is to search for a relation between rotator cuff tear size and degree of SSN recovery. The tertiary objective is to demonstrate any relation between rotator cuff muscle fatty infiltration grade and degree of SSN function.

## Methods/design

This study will be a single-center, double-blinded randomized controlled trial (RCT). The trial is registered at the ClinicalTrial.gov website, number NCT02318381. The Institutional Review Board of “Georgios Papanikolaou” Hospital has provided ethical approval. The study will be conducted in accordance with the Helsinki Declaration. All patients will be provided with a written Consent Form that they will have to sign in order to be considered for this study. The study’s Consolidated Standards of Reporting Trials (CONSORT) flowchart and Standard Protocol Items: Recommendations For Interventional Trials (SPIRIT) figure can be found in Fig. 1 and Table 1, respectively. The SPIRIT checklist has been added as Additional file 1 to this protocol.

**Fig. 1 Fig1:**
[figure not shown]
Study flowchart

**Table 1 Tab1:** Standard Protocol Items: Recommendations for Interventional Trials (SPIRIT) diagram

	Study period					
	Enrollment	Allocation	Post allocation			
Time point	Preintervention	Time 0	Baseline (Intervention)	Post intervention	6-month follow-up	12-month follow-up
Enrollment:						
Eligibility screen	X					
Informed consent	X					
Allocation		X				
Interventions:						
Control group: repair of rotator cuff *only*			X			
Second group: repair of rotator cuff and SSN release			X			
Assessments:						
NC/EMG studies	X				X	X
Clinical shoulder assessment/signs	X			X	X	X
Constant-Murley score	X				X	X
DASH score	X				X	X
ASES score	X				X	X
MRI scan	X					X

*ASES* American Shoulder and Elbow Surgeons, *DASH* Disabilities of the Arm, Shoulder and Hand, *EMG* electromyography, *MRI* magnetic resonance imaging, *NC* nerve conduction, *SSN* suprascapular nerve

### Trial objectives/endpoints

The primary endpoint of this study will be recording of changes of function of the SSN, as assessed by electromyography (EMG) and/or nerve conduction (NC) studies, preoperatively, and at 6 and 12 months postoperatively. All NC/EMG studies, pre and postoperative, will be performed by one neurologist for all included patients. Clinical signs of full recovery will also be assessed and compared pre and postoperatively.

Abnormal function of the SSN in EMG studies will be indicated by fibrillation and high-frequency discharge potentials. An abnormal NC assessment finding is defined according to the following values: infraspinatus latency >4.5 ms and an amplitude <8 mV from peak to peak and supraspinatus muscle latency >3.5 ms and an amplitude <8 mV from peak to peak [12]. The contralateral nerve will also be examined. Abnormal findings are also indicated when the difference in amplitude compared to the healthy side is more than 50%. According to patients’ results, the NC/EMG studies postoperatively will show full recovery of the nerve if all parameters are normal and partial recovery if the tested parameters are improved but not normalized. It is possible, due to some patients’ habitus and size, that NC studies may not be feasible to perform on these patients. In these cases, diagnosis will be established by EMG studies.

The secondary endpoint will be analyzing for possible correlations between tear size, SSN neuropathy frequency, and degree of postoperative nerve recovery. The diameter of the tear will be measured preoperatively with a ruler by using standardized MRI sagittal images. Measurement starts at the insertion of the tendon into the major tuberosity and ends at the most lateral margin of the torn rotator cuff. Only the largest measured diameter of the tear as found on images will be recorded.

The tertiary endpoint will be analyzing the rotator cuff muscles for changes of fatty infiltration as assessed using MRI studies (according to Goutallier’s classification) before and 12 months after the operation [13]. Goutallier classified fatty infiltration as: stage 0, normal muscle; stage 1, some fatty streaks; stage 2, less than 50% fatty muscle atrophy; stage 3, 50% fatty muscle atrophy; stage 4, greater than 50% fatty muscle atrophy.

### Study population

Forty-two patients with SSN neuropathy and repairable large or massive rotator cuff tears will be recruited according to the inclusion/exclusion criteria of this RCT, divided in two equally numbered groups and treated within a 24-month period at the First Orthopedic Department of Aristotle University of Thessaloniki, “Georgios Papanikolaou” Hospital, Greece. Inclusion criteria are: patients with large or massive repairable rotator cuff tears combined with SSN neuropathy on the ipsilateral side. Exclusion criteria are: SSN neuropathy of another cause (e.g., brachial plexus neuropathy), other previous surgery performed on the same affected shoulder, and moderate to severe degenerative changes to the ipsilateral glenohumeral joint (rotator cuff arthropathy).

All patients seen in our institution’s shoulder clinic with MRI-confirmed large or massive repairable rotator cuff tears and suspected SSN neuropathy will undergo NC/EMG studies in order to establish a diagnosis of the neuropathy. Patients with no signs of pain, atrophy, or paresthesia over the SSN distribution area, or patients who refuse to have any more diagnostic processes, will not have NC/EMG studies and will not be considered for the study. If the above studies are positive for SSN neuropathy, and the patients meet the inclusion and none of the exclusion criteria, they will be informed about this trial. If they agree to participate in this trial and sign and date the informed consent, then a further preoperative appointment will be given.

An investigator will clinically examine the patients on the second preoperative appointment. A specific form will be created for each one that will contain demographic, preoperative, and postoperative data (Additional file 2: Table S1). All patient forms will additionally be kept in electronic records for easier data analysis. Randomization and allocation of patients to a specific group will be done by the statistician. All patients, the clinical preoperative and follow-up examiner, and the neurologist performing the NC/EMG studies will be blinded to the type of surgery performed.

The first group of this trial will be the control group and will consist of 21 patients; these will undergo arthroscopic repair of the rotator cuff tear. The second group will also consist of 21 patients. They will undergo the procedure as above, along with an arthroscopic release of the SSN at the same stage.

### Details of preoperative and postoperative examinations

All patients’ demographic data (age, gender, occupation, allergies, smoking status, alcohol consumption) and medical history will be recorded preoperatively. Patients will be examined for specific clinical signs such as Hornblower’s sign, the dropping sign, Jobe’s test, Hawkins test, and the lag sign. Shoulder range of motion (ROM) and shoulder power of the rotator cuff muscles of both arms will also be examined.

The Constant-Murley [14], Disabilities of the Arm, Shoulder and Hand (DASH) [15], and American Shoulder and Elbow Surgeons (ASES) [16] scores will be recorded. The Constant-Murley shoulder score has a 100-point scale and is a commonly used outcome measure for assessing the outcomes of the treatment of shoulder disorders. It includes a pain score, functional assessment, and ROM and strength measures (0 worst score, 100 best score). The DASH outcome measure has 30 questions, which are scored from 1 to 5 according to the severity of a patient’s symptoms (0 best score, 100 worst score). The optional modules of this score will not be measured as, according to our previous experience, most patients will not be professional athletes, musicians, or high-demand workers. Also, this will facilitate an easier comparison of scores between patients. The ASES score is another patient-reported questionnaire and has 17 questions. The first seven of these explore the intensity and type of pain up to a total of 50 points and the rest measure functionality of the shoulder and add another 50 points (0 worst score, 100 best score).

### Study procedure

Patients will be randomized on the admission day and allocated to a group, so that they may undergo arthroscopic rotator cuff repair alone, or combined with arthroscopic release of the SSN. Only the operating surgeon, who will be the same for all patients, will be aware of the randomization results and patient allocation list.

All patients are going to be treated according to the established institutional protocol and the operation will follow well-defined standards in order to minimize adverse factors. All operations will be done with the patient in a beach-chair position, under general anesthesia and with a regional (interscalene) anesthetic block for postoperative analgesia. If general anesthesia is contraindicated, then the procedure will be done with the patient awake or mildly sedated and with the regional block as the main anesthetic agent; these patients will be recorded. Prepping will be done as per hospital protocol with aqueous povidone iodine 7.5%, and draping will be the same for all patients. Standard portals will be made for all patients: posterior, anterior, lateral, and anterolateral; a superior portal will additionally be made for patients undergoing release of the superior transverse scapular ligament.

The procedure will aim at fully restoring the rotator cuff to its anatomical footprint. When the cuff is not repairable then these patients will be excluded from the study. If during the operation the surgeon fails to fully repair the cuff and achieves only a partial repair, these patients will be recorded and followed up but separated from the cohort; their outcomes will be compared with those of the rest. All repairs will be done using a transosseous equivalent technique with peek anchors, knotted medially and knotless laterally. Arthroscopic release will follow the technique published by Lafosse et al. [1]. Visualization will be done mostly by the lateral portal and the shaver will mostly work through a lateral-anterolateral portal. The transverse ligament will be dissected via a superior portal, which is created under direct vision and uses a needle to identify the exact location of the portal.

As per the surgical protocol, all patients will also undergo tenotomy of the long head of biceps and acromioplasty with excision of the coracoacromial ligament. Also, excision of the acromioclavicular joint will be performed only if patients complain of pain in that region along with degenerative changes being shown on X-rays, or found intraoperatively. If any further lesions are detected during the operation, the surgeon will proceed to repair them and such incidents will also be recorded. Skin closure will be performed with 3.0 nylon sutures. Nonadhesive dressings and pressure dressings will be applied to the top of the shoulder and patients will be placed in a 30^o^ abduction sling immediately after completion of surgery.

Patients will stay overnight at the hospital. Physiotherapists will advise them as per the physiotherapeutic protocol (Table 2). The abduction sling will remain for the first 6 weeks. Sutures will be removed 10 days after surgery. Outpatient and physiotherapy clinic follow-up will be arranged at 6 weeks, 3 months, and 6 and 12 months postoperatively. Neurology clinics for NC/EMG studies will be arranged at 6 and 12 months postoperatively. Outcome scores will be collected at 6 and 12 months after surgery.

**Table 2 Tab2:** Brief physiotherapy protocol for postoperative rehabilitation of repaired large/massive rotator cuff tears

Time	Focus	Range of motion	Recommended exercises	Precautions
0–6 weeks	Tissue healing	No passive assisted or active ROM of shoulder allowed apart from table slides	• Restricted table slides after 2nd week to 30° • AROM of elbow, wrist, hand	• No active reaching • Sling at all times
6–12 weeks	PROM, AAROM with transition to AROM	Regain full PROM and AAROM, transition to AROM at 10 weeks	• PROM of shoulder, pendulums, scapular mobility, ball squeeze begin AAROM at 8 weeks • Isometrics and active progression at 10 weeks	• No resisted activity and lifting • Avoid overloading of supraspinatus • Must regain scapular rhythm before transition to strengthening
12–24 weeks	AROM and progressive strengthening	Regain full AROM	• Continue PROM and AAROM as needed • Initiate strengthening and progress AROM to functional planes • Progress proprioceptive drills, rhythmic stabilization, push-ups, resistance band	• No heavy or repetitive overhead activities • Limited return to gym after 20th week if AROM with satisfactory scapular rhythm has been achieved • Free full ROM
24 weeks–1 year	Return to sports and physical activity if ROM and strength adequate		• Progression of strengthening • Continue resistance band, proprioceptive drills and periscapular stabilization until full return to physical activity and sports	• Return to sports • Progress gym lifting

*AAROM* active assisted range of motion, *AROM* active range of motion, *PROM* passive range of motion, *ROM* range of motion

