#### Randomization/blinding

The choice of resecting or not the transverse scapular ligament will be done in a randomized manner. Randomization will be made by using the Microsoft Office Excel program and its RAND function. Forty-two cells will be created and the numbers in them will be rounded up so that they have no decimals. Odd numbers will create the first group and even numbers will create the second group. If RAND function fails to create even groups, it will be redone until even groups of odd and even numbers are achieved. Patients will be placed at each consecutive cell at the time of recruitment, after inclusion in this trial, and will be randomized by the statistician. The surgeon will be informed about the type of treatment needed for patients on the admission day. This will be facilitated with opaque envelopes containing the patient’s group, which the primary investigator will have received from the statistician. The primary investigator will place this envelope inside the patient’s physical records just before the patient is taken to the operating room. An operating department practitioner nurse will open the envelope just after the surgeon finishes the rotator cuff repair and will instruct him, according to the patient’s group, whether to release the ligament or not. By doing this, the surgeon will not be biased by knowing the patient’s group before repairing the cuff (avoidance of performance bias).

The surgeon, therefore, clearly cannot be blinded to the type of procedure, but this will not bring any bias to the study. Patients, physiotherapists, and the clinician measuring outcomes will be blinded to each patient’s allocated treatment. The neurologist will also not know the type of surgery performed. This blinding will assist in obtaining objective results while performing NC/EMG studies and should exclude such bias.

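### The protocol gives the operating surgeon the allocation list in one section and, in another, relies on the surgeon not knowing the arm until the cuff repair is finished; the two texts must be reconciled.

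*Protocol article*

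**What the plan says.** Four places in the protocol article bear on who knows the allocation and when.

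- **Study procedure**, on knowledge: "Only the operating surgeon, who will be the same for all patients, will be aware of the randomization results and patient allocation list". No time limit is attached. On timing, the same paragraph says: "Patients will be randomized on the admission day and allocated to a group".
- **Study population**, on who allocates: "Randomization and allocation of patients to a specific group will be done by the statistician".
- **Randomization/blinding**, on the list: 42 spreadsheet cells, regenerated until the two groups are equal. "Patients will be placed at each consecutive cell at the time of recruitment", with the statistician again doing the randomizing.
- **Randomization/blinding**, on disclosure: "The surgeon will be informed about the type of treatment needed for patients on the admission day". The text then explains that this works through opaque envelopes, which go from the statistician to the primary investigator and into the patient's records shortly before theatre. "An operating department practitioner nurse will open the envelope just after the surgeon finishes the rotator cuff repair and will instruct him". The stated purpose is that "the surgeon will not be biased by knowing the patient’s group before repairing the cuff (avoidance of performance bias".

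The same section accepts that the surgeon cannot be blind to the procedure and asserts that this introduces no bias.

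**The concern.** The late opening of the envelope is the only safeguard described that keeps the surgeon unaware of the arm during the repair. The assurance that an unblinded surgeon brings no bias rests on it. A surgeon who already holds the list gains nothing from a sealed envelope.

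This matters more than usual here because one surgeon performs every operation and also makes the intraoperative judgments that decide a patient's place in the analysis. A surgeon who knows the arm could, without intending to, vary the effort put into the repair or lean one way in a borderline judgment. Blinding the patients, the clinical examiner and the neurologist protects the measurement of outcomes. It does not protect against either of these.

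**Working it through.** The point rests on no figure, so the check is a comparison of texts.

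**Step 1. Who knows the allocation, and when?**

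| Section | Who has the allocation | When the surgeon learns the arm |
|---|---|---|
| Study population | Statistician allocates | Not stated |
| Study procedure | Surgeon alone knows results and list | No limit; the list implies before surgery |
| Randomization/blinding, admission-day sentence | Statistician | Day of admission |
| Randomization/blinding, envelope steps | Statistician, then an envelope per patient | After the repair, from the nurse |

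The second and fourth rows are incompatible: knowing the list means knowing the arm before the repair. The second row also conflicts with the first, since the statistician who allocates must know the results. The third row is weaker evidence (see the objection).

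**Step 2. What would the list reveal?** It is a fixed sequence of 42 cells, balanced 21 to 21, and patients take the cells in order. Whoever holds it can read the current patient's arm and the arms of patients still to come.

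**Step 3. Which surgeon judgments come before the envelope is opened?**

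- Cuff not repairable: the patient is excluded (Study procedure) or withdrawn (Subject withdrawal).
- Only a partial repair achieved: the patient is followed up, set apart from the main cohort and compared with it (Study procedure).
- Moderate or severe arthropathy found at surgery: the patient is withdrawn (Subject withdrawal).

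Under either stated time of randomization, these judgments fall after it. Under the envelope text they are made without knowledge of the arm. Under the Study procedure sentence they are made with it.

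**Step 4. When is a patient randomized?** Study procedure says the admission day. Randomization/blinding places the patient in a cell at recruitment and has the statistician randomize. The two differ, so it is unclear whether a patient lost between recruitment and admission counts as randomized. The SPIRIT diagram shows allocation at Time 0, before the intervention, which does not settle the choice.

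**Step 5. Does resolving this change the sample size?** No. The planned 19 per group (38 in total, raised to 42 for losses) does not depend on who knows the list.

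**The case against.** The strongest reply is that the Study procedure sentence is a loose summary of who ends up unblinded. It cannot be literally true that only the surgeon knows, because the statistician allocates and a nurse reads the envelope. The Randomization/blinding section is the dedicated, step-by-step text, and it states its purpose. That may well be what was intended. But the sentence names the allocation list and sets no time limit, so the conflict stands as written.

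Parts of the reply do succeed, and they limit the point:

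- **The admission-day sentence.** A reader might take it as a second, independent contradiction. The sentence that follows it introduces the envelopes, so it may be only a lead-in to that procedure. It needs rewording, but the point does not depend on it.
- **Three allocation times.** A reader might count recruitment, admission and envelope opening. Opening the envelope discloses an assignment already made; it does not make one. Only recruitment and admission day need aligning.
- **Selection bias at enrolment.** A reader might infer it from the surgeon holding the list. No section says that the surgeon enrols patients. Eligibility rests on imaging, nerve studies and consent, and patients enter the list after inclusion.
- **Every intraoperative judgment removing a patient.** Partial repairs are still followed up and compared under Study procedure, so this overstates the text.

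**Conclusion.** The contradiction is real and should be corrected. The Study procedure sentence cannot stand beside the envelope procedure, and following it would defeat the protocol's own protection against performance bias and let exclusions after randomization depend on the arm. The consequence is conditional: if the envelope steps alone are followed, the surgeon does not learn the arm before the repair is complete.

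The size of any bias cannot be derived from the documents. They give no expected number of intraoperative exclusions and no basis for how far knowledge of the arm would alter them. A reader might infer that one discretionary exclusion would decide the trial. The document does not support that, because the effect depends entirely on which hypothetical results table is chosen. What can be said is that one surgeon treats all 42 planned patients, so whichever text is followed applies throughout the trial.

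The conclusion assumes that the two sections describe the same trial procedure and that the list sentence means what it says. The trial is reported as recruiting, and concealment once lost cannot be restored in the analysis.

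**What to change.** 1. In Study procedure, replace the sentence about the surgeon and the list. State that only the statistician holds the list and that the surgeon learns each assignment only when the envelope is opened after the repair.
2. In Randomization/blinding, reword the admission-day sentence so that it describes the envelope's route and not disclosure to the surgeon.
3. State one time of randomization and use it in both sections.
4. Have the surgeon record arthropathy and repair status before the envelope is opened, so that these judgments can be shown to have been made without knowledge of the arm.
5. For patients already treated, document which text was followed.

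Items 1 to 3 cost only wording. Item 4 costs one line on the intraoperative form. Item 5 needs a short note to file. The envelopes and the nurse are already in place, and the sample size does not change.

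Making the opening of the envelope the moment of randomization is possible, but the contradiction can be resolved without it. The fix does not reach withdrawal for failure to release the nerve (Subject withdrawal), which can arise only in the release arm after the envelope is opened. That is a separate matter.

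### Only release patients receive a superior portal, and nothing described hides its scar from the assessors who are said to be blinded

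*Protocol article*

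**What the plan says.** **Portals.** Under Study procedure: "Standard portals will be made for all patients: posterior, anterior, lateral, and anterolateral". The same sentence continues that "a superior portal will additionally be made for patients undergoing release of the superior transverse scapular ligament". No matching incision is described for controls.

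**Blinding claim.** The Abstract and Study population sections say that patients, the clinical examiner and the neurologist are blinded to the type of surgery. Randomization/blinding adds physiotherapists. It says of the neurologist: "The neurologist will also not know the type of surgery performed". It then concludes: "This blinding will assist in obtaining objective results while performing NC/EMG studies and should exclude such bias".

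**Wound care and timing.** The continuation of Study procedure describes dressings on top of the shoulder straight after surgery, suture removal at 10 days, and NC/EMG studies and outcome scores at 6 and 12 months. No later covering is described.

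**Concealment steps.** Randomization/blinding describes opaque envelopes, opened by a theatre nurse once the cuff repair is finished. The stated purpose is to keep the surgeon from knowing the arm during the repair.

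**The concern.** The concealment steps protect the repair, which comes before allocation is revealed. They do nothing about what can be seen afterwards. The extra incision lies in the shoulder region that the examiner and the neurologist both assess, and it occurs in one arm only. Someone who sees it and knows what it means can infer the arm.

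What is at stake is detection bias in the parts of the outcome that need judgment. Under Trial objectives/endpoints, abnormal EMG is defined by fibrillation and high-frequency discharges, which the operator has to recognise. EMG alone establishes the diagnosis where NC studies are not feasible. Full recovery requires every parameter to be normal, so one judged parameter can decide a patient's classification. The Discussion itself concedes that NC/EMG lacks clear criteria for this diagnosis. One neurologist performs every study, so the same person would see both scar patterns repeatedly: with full attendance, 42 patients × 2 postoperative visits = 84 studies.

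**Working it through.** **1. The two statements side by side.**

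| | Control | Release |
|---|---|---|
| Patients planned | 21 | 21 |
| Standard portals | 4 | 4 |
| Superior portal | 0 | 1 |
| Portals in total | 4 | 5 |
| Covering described at 6 and 12 months | none | none |

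The arms differ by one incision in every release patient treated as planned. The only covering described is the immediate postoperative dressing. A claim that assessors do not know the arm therefore rests on their not noticing or not interpreting the scar, because no procedure prevents it.

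**2. Which outcomes are exposed.**

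- Latency and amplitude have numeric cut-offs (infraspinatus latency above 4.5 ms, supraspinatus above 3.5 ms, amplitude below 8 mV, side difference above 50%). These leave less room for judgment.
- Needle EMG discharges are read by the operator. They are exposed if the neurologist infers the arm.
- Constant-Murley combines pain and function with range of motion and strength. The examiner-rated part is exposed if the examiner infers the arm.
- DASH and ASES are completed by the patient. They are exposed if the patient infers the arm.

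**3. The plan's own sample size.** Inputs from Sample size calculation: full recovery 100% with release and 66.67% without, alpha 0.05, power 0.8, Fisher's exact test, equal allocation. If all 19 release patients recover and k controls do not, the two-sided p-value is 2 × C(19,k)/C(38,k).

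| k | Controls recovered | Two-sided p |
|---|---|---|
| 4 | 15/19 | 2 × 3,876/73,815 = 0.105 |
| 5 | 14/19 | 2 × 11,628/501,942 = 0.046 |
| 6 | 13/19 | 2 × 27,132/2,760,681 = 0.020 |
| 7 | 12/19 | 2 × 50,388/12,620,256 = 0.008 |

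Significance needs k of 5 or more. Summing the binomial probabilities over those values gives power 0.812 at 19 per group (0.769 at 18), so the stated 38 patients reproduce.

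**4. What misreading could do.** The documents give no rate of unblinding and no size of bias, so this is illustration only. Assume true full recovery of 66.67% in both arms and 19 per group, and let knowledge of the arm raise the recorded release-arm rate by a fixed amount:

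| Assumed shift (percentage points) | Chance of a significant result, two-sided Fisher |
|---|---|
| 0 | 2.5% |
| 5 | 3.2% |
| 10 | 5.7% |
| 15 | 10.7% |
| 20 | 20.0% |

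Under this assumption the false-positive rate passes 5% at a shift of about 10 points. Nothing in the documents says whether a shift of that size, or any shift, would occur.

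**The case against.** The best defence is that an article condenses a fuller protocol, that the primary endpoint rests partly on numeric cut-offs, and that one small arthroscopic scar among five may mean little to an assessor at 6 or 12 months. Part of this stands. The documents do not record how visible the scar is, and the cut-offs limit the room for bias. The point is not one of mere omission, however: the article itself states both the arm-specific incision and the claim that blinding should exclude bias, and the concealment steps it describes in some detail do not connect the two.

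Four stronger readings are tempting and are not supported.

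- *The envelope unblinds the assessors.* It is placed in the patient's "physical records just before the patient is taken to the operating room", but it is opaque and is opened in theatre. Nothing says that the opened slip stays in the chart or that assessors use that chart. Study population describes a separate data form and electronic records. This is a route left unguarded, not a shown breach.
- *Patients overhear their allocation.* The relevant text is "If general anesthesia is contraindicated, then the procedure will be done with the patient awake or mildly sedated". This is an exception to general anesthesia, the number of such patients is not given and may be zero, and the text does not say that the nurse's instruction is audible.
- *Every release patient is unblinded.* The documents support an extra incision in every release patient. They do not show that anyone recognises it.
- *One borderline reading decides the trial.* Moving from 15/19 to 14/19 control recoveries does cross 0.05. That example sits at the boundary. Near the planned rate (19 × 0.6667 = 12.7, about 13/19), p is 0.020, and reclassifying one control as recovered gives 0.046, still significant. Sensitivity to one patient at the threshold belongs to any small Fisher test and does not measure blinding bias.

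Two further objections stand. Constant-Murley, DASH and ASES are not named among the primary, secondary or tertiary endpoints. And a dressing at visits cannot stop patients from seeing their own shoulder at home, so the remedy can protect assessor blinding only.

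**Conclusion.** The concern holds in this form: the procedures described do not secure the blinding that the article claims, because only release patients receive the superior portal and nothing conceals its scar when outcomes are read at 6 and 12 months. The incision difference applies to all 21 planned release patients. How many people would infer the arm, and how far that would move the results, cannot be derived from the documents; the shifts of 5 to 20 points above are assumptions. Needle EMG and the examiner-rated part of Constant-Murley are the main exposure, and the latency and amplitude cut-offs less so. The envelope and awake surgery are secondary routes worth closing, and the conclusion does not depend on them. Because the bias is unquantified, the endpoint partly objective and the remedy cheap, this should be fixed but does not by itself invalidate the trial.

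**What to change.** Add to Randomization/blinding:

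1. Before each outcome visit, the superior portal site of every patient, in both arms, is covered with the same opaque dressing. Existing staff who do not assess outcome apply it, or the patient does. Electrodes and needles are placed around it.
2. The opened allocation slip and the operative note are kept out of any file that the examiner or the neurologist uses.
3. When a patient is awake or mildly sedated, the nurse shows the allocation to the surgeon silently.
4. The blinding claim is restated: the examiner and the neurologist are blinded by these measures, while patients may infer their arm from the scar, so DASH and ASES are to be read with that in mind.

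Asking the patient, examiner and neurologist to guess the arm at 12 months is optional. It would inform the report but prevents no bias.

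The cost is a dressing and about a minute per visit, slight inconvenience in electrode placement, and a less favourable statement about patient blinding. The surgery is unchanged. The article describes the trial as still recruiting, so the measures could begin at the next visits.
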